### Plans to promote participant retention and complete follow-up (18b)

The following information is collected via a locator form to minimize loss to follow-up: name, personal health number or patient identification number (depending on whether the participant has access to provincial care in Quebec or Medicaid in Florida), date of birth, the best numbers, ways, day and time to reach them, if text messaging is acceptable, email address, names of relatives and friends who would know how to reach them, and permission to contact them for that purpose, the name of the doctor or community health center that would know how to reach them, parole officer contact information (if relevant), permanent physical address (if available) alternative living situation and address, usual hangouts, access to other organizations where a message can be left. In addition, participants are compensated for their time and effort for baseline, DBS, intervention, and follow-up visits. Compensation is issued in cash, gift card, or electronic payment. Maximum compensation for participants over their 18-month participation is US $440 in the Miami sites and Canadian $455 in the Montreal sites.

### Data management (19)

Data management is coordinated using REDCap tools hosted at the University of Miami using a confidential and secure database management system that includes consistency and range checks [66, 67]. The data management team is responsible for the development and validation of the clinical study database, ensuring data integrity, and training site staff on applicable local data management procedures. To address the issue of data entry quality, the data management team follows a standard data monitoring plan. If the data management team finds incomplete or inaccurate data, a data clarification request is generated and distributed to sites for a response. An acceptable quality level prior to study data lock or closeout will be established as a part of the data management plan.

### Confidentiality (27)

All assessments, study forms, and other records are coded using research identity (RID) numbers only. All research and clinical records are stored in a secured location with limited access. Records that have personal identifiers are stored separately from research records that contain only the participants’ RID number. This includes consent forms, clinical records, and files that link participants’ names with RID numbers. The study automatically received a Federal Certificate of Confidentiality (CoC) from the National Institutes of Health (NIH) to protect against any demands for information that would identify participants. Exceptions to confidentiality for participants are disclosures required by law, including reportable disease. Participants are informed of these exceptions in the informed consent process.

### Plans for collection, laboratory evaluation, and storage of biological specimens for genetic or molecular analysis in this trial/future use (33)

Most specimen collected during this study is a regular blood test, such as CBC, that will be collected and destroyed as per local laboratory procedures. The two exceptions are the DBS for TDF/FTC detectability and a serum sample.

DBS are collected to assess the detectability of TDF/FTC monthly for the first 6 months post-randomization (commencing at 8 weeks post-PrEP initiation) and every 3 months thereafter. After collection, specimens are left to dry for 4–24 h. Dried samples are then placed in individual plastic bags with two desiccant bags and a moisture indicator cardboard. Samples are transported at 4°C and kept frozen at −70°C. Liquid chromatography and mass spectroscopy will be used to detect the presence of tenofovir-diphosphate on DBS [61, 62].

For patients who are HCV RNA positive at baseline, a serum is kept frozen at −80°C for the duration of the study. This specimen will be used to distinguish, through sequencing, between treatment failure and reinfection in case of re-occurrence of HCV RNA positivity after treatment. All specimen will be destroyed as per local procedure at the end of the study.

## Statistical methods

### Statistical methods for primary and secondary outcomes (20a)

The *primary hypothesis* is that on-site integrated care is superior to off-site referral with patient navigation in achieving higher rates of sustained PrEP adherence and/or HCV cure, measured as the proportion of participants achieving detectable levels of tenofovir in DBS in the first 6 months of follow-up and achieving HCV sustained virologic response 12 weeks post-treatment completion after initiating treatment within the 6 months post-randomization. A sub-hypothesis is that the difference in rates of sustained PrEP adherence and HCV cure with on-site integrated care relative to referral with patient navigation will be moderated by healthcare system and venue; differences between on-site versus referral will be greater in Miami vs. Montreal and in SSP vs. OAT settings. For the *primary hypothesis*, each of our two co-primary outcomes, sustained PrEP adherence and HCV cure, will be tested at an alpha rate of .025 using a Poisson regression analysis with a binary outcome to directly estimate the risk ratio associated with on-site integrated care (rather than the odds ratio estimated by logistic regression). Both co-primary hypothesis tests will be stratified by site and venue, testing for interactions of treatment effect by site and venue due to our expectation that context is important for implementation. In the absence of qualitative interaction effects, the main effects will be examined.

We will analyze long-run sustained PrEP adherence and HCV cure resulting from treatment initiated after the first 6 months, similarly, except using a repeated-measures Poisson regression implemented as a generalized estimating equation (GEE) including the periods between 6- and 18-month follow-ups. It is important to note that for all PrEP adherence analyses, any participants who become HIV positive will be counted as PrEP non adherent. For all other secondary outcomes, similar approaches will be used. PrEP initiation will be assessed as a simple binary outcome (initial self-reported use verified by prescription in medical records) and again modeled using repeated measures Poisson regression. We will examine sustained PrEP adherence among those self-reporting taking PrEP to disentangle PrEP non-engagement, inadequate PrEP use, and protective levels of PrEP use. Note that protective levels of PrEP use will be examined only among patients not on HCV medication due to norms for protective PrEP use when taken with HCV medication not having been established. We will examine HCV treatment initiation and rates of SVR among those treated (the primary analysis will include all HCV-positive randomized participants). We will examine potential rates of behavioral disinhibition as measured by changes in self-reported sexual risk (i.e., condom-less vaginal and/or anal sex), needle/works sharing, HCV infection/re-infection rates, and STI (including HIV) infection rates over the entire follow-up period. Additional analyses will examine the timing of initiation of both PrEP and HCV treatment, and whether non-engagement and discontinuation of PrEP are related to levels of (or changes in) risk.

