**Methods:**

The Miami-Montreal Hepatitis C and Pre-Exposure Prophylaxis trial (M^2^HepPrEP) is an open-label, multi-site, multi-center, randomized, controlled, superiority trial with two parallel treatment arms. A total of 500 persons who injected drugs in the prior 6 months and are eligible for PrEP will be recruited in OAT clinics and SSP in Miami, FL, and Montréal, Québec. Participants will be randomized to either on-site care, with adherence counseling, or referral to off-site clinics assisted by a patient navigator. PrEP will be offered to all participants and HCV treatment to those HCV-infected. Co-primary endpoints will be (1) adherence to pre-exposure prophylaxis medication at 6 months post-randomization and (2) HCV sustained virological response (SVR) 12 weeks post-treatment completion among participants who were randomized within the HCV stratum. Up to 100 participants will be invited to participate in a semi-structured interview regarding perceptions of adherence barriers and facilitators, after their 6-month assessment. A simulation model-based cost-effectiveness analysis will be performed to determine the comparative value of the strategies being evaluated.

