### Outcomes (12)

#### Primary outcome measures

The co-primary trial outcomes are (1) sustained PrEP adherence during the first 6 months and (2) HCV cure among participants living with HCV.

**Table 4 Tab4:** Definition and measure of secondary and tertiary outcomes

Secondary outcomes	Definition	Measure
PrEP initiation/uptake	Receiving a prescription and taking the first dose of the medication	First dose of Rx dispensed to the patient and recorded at pharmacy/dispensing venue + self-report
Long-term sustained PrEP adherence	PrEP use at 6, 12, and 18 months post-randomization	Self-report + detectable level of TDF in DBS 6, 12, and 18 months post-randomization
HCV incidence/re-infection	New HCV infection	At scheduled visit: HCV-Ab positive (never infected) or detectable HCV-RNA (previously infected and cured)
STI or HIV incidence/STI re-infection	New STI or HIV infection in a previously uninfected person/previously infected and cured person	At scheduled visit: Any positive test result for *Neisseria gonorrheae*, *Chlamydia trachomatis*, syphilis, or HIV
Behavioral disinhibition	Changes or increase in sexual or injection risk behaviors	Self-report at each visit
**Tertiary outcomes**	**Definition**	**Measure**
Ongoing PrEP use	Any PrEP use during any period	Any detectable level of TDF in DBS/Self-report of use
HCV SVR within those initiating	12-week sustained viral response post-end of treatment	First dose of medication dispensed to the patient and recorded at pharmacy/dispensing venue + self-report/HCV-RNA negative at 12 weeks post end of treatment

Sustained PrEP adherence will be compared between both treatment arms at 6 months post-randomization. Sustained PrEP adherence will be defined as the self-report of achieving daily PrEP use, which will be confirmed by evidence of detectable levels of tenofovir. In order to achieve protection against HIV infection, TDF/FTC should be taken once daily to achieve protective levels. PrEP use will be self-reported by participants. Blood tenofovir will be detected using DBS collected every month beginning at 8 weeks post-PrEP initiation during the first 6 months post-randomization and subsequently every 3 months during research visits.

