## Data collection and management

### Plans for assessment and collection of outcomes (18a)

Data collection is planned at screening, baseline, and every 3 months thereafter. “Full” research follow-up visits occur at approximately 6, 12, and 18 months post-randomization while participants have short interim research visits approximately 3, 9, and 15 months post-randomization. In the first 6 months post-randomization, participants are scheduled for DBS monthly after 8 weeks of initiating treatment if on PrEP. Pregnancy tests will be required at each research visit for all randomized participants of child-bearing potential. Tables 2 and 3 describe the battery of assessments and lab assessments planned.

Assessments are administered in a private space by a trained interviewer through a computer-assisted personal interview (CAPI) or through paper case report forms (CRF) that are later entered into an electronic data capture (EDC) system. Self-report questionnaires are programmed in REDCap and administered from a password-protected website. Wherever possible, we use measures from NIDA’s Data Harmonization projects (e.g., Seek, Test, Treat and Retain [64]) or established PrEP studies (e.g., the PrEP Demo Project) [65]. Assessments are interviewer-administered; the initial assessment will take approximately 90 min and others 45–50 min.

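### The PrEP co-primary has two incompatible definitions, two time frames and an unreconciled DBS sampling schedule; the version that is tested does not measure daily adherence

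*Protocol article*

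**What the plan says.** The protocol article describes this outcome in several places.

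- **Outcomes (12), Primary outcome measures.** Sustained PrEP adherence is "defined as the self-report of achieving daily PrEP use, which will be confirmed by evidence of detectable levels of tenofovir". The outcome is introduced as covering the first six months, and then: "Sustained PrEP adherence will be compared between both treatment arms at 6 months post-randomization".
- **Statistical methods (20a), primary hypothesis.** The outcome is "measured as the proportion of participants achieving detectable levels of tenofovir in DBS in the first 6 months of follow-up", with no self-report and no daily-use element.
- **Abstract, Methods.** The co-primary is "adherence to pre-exposure prophylaxis medication at 6 months post-randomization". Objectives (7) gives 0–6 months.
- **Table 4, tertiary outcomes.** Ongoing PrEP use, meaning any use in any period, is measured by "Any detectable level of TDF in DBS/Self-report of use".
- **Sampling.** Section 18a says "participants are scheduled for DBS monthly after 8 weeks of initiating treatment if on PrEP". Outcomes (12), Assessment of outcomes and the specimen section (33) also start DBS 8 weeks after PrEP initiation. Table 2 marks DBS at baseline, weeks 8, 12, 16 and 20, month 6, and three-monthly after that.
- **Additional analysis (20a).** Among self-reported takers, the plan will "disentangle PrEP non-engagement, inadequate PrEP use, and protective levels of PrEP use".

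**The concern.** A co-primary that carries half of the alpha should be one variable. Here two rules give different answers for an identifiable group: people with drug in the blood who do not report taking it daily. The planned additional analysis shows that the authors expect such people, because it separates inadequate from protective use.

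Under the 20a rule, a positive trial would show that more on-site participants had taken some PrEP. The article would report this as better sustained adherence.

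The sampling schedule adds a second problem. If samples are counted from PrEP initiation, the number a person can contribute by month 6 depends on how quickly PrEP was started. Speed of initiation is something the two arms may change.

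**Working it through.** **1. The plan's own figure.** Inputs from Sample size (14) and Sequence generation (16a): 500 participants, 1:1, so 250 per arm; alpha .025, taken as two-sided (z = 2.241); 40% versus 55.5%.

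- Pooled rate = (0.40 + 0.555)/2 = 0.4775. Null SE = √(2 × 0.4775 × 0.5225/250) = 0.0447.
- Alternative SE = √((0.40 × 0.60 + 0.555 × 0.445)/250) = 0.0441.
- Power = Φ((0.155 − 2.241 × 0.0447)/0.0441) = 0.893.

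The stated 90% reproduces. The section does not say which definition the 40% and 55.5% refer to.

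**2. The definitions side by side.**

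| Participant in the first 6 months | Outcomes (12) rule | 20a rule |
|---|---|---|
| Reports daily use, drug detectable | success | success |
| Does not report daily use, drug detectable | failure | success |
| Reports daily use, drug not detectable | failure | failure |

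The rules differ only in the second row. Its size is not given, so it has to be assumed.

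**3. What the second row does to the result.** Let p be the success rate under the Outcomes rule, and f the share of the remaining participants with detectable drug. The 20a rate is p + f(1 − p). If 40% and 55.5% are rates under the Outcomes rule and f is equal in both arms, the difference becomes 15.5 × (1 − f) points:

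| f (assumed) | 20a rates | Difference (points) | Power |
|---|---|---|---|
| 0 | 40.0% vs 55.5% | 15.5 | 0.89 |
| 0.1 | 46.0% vs 60.0% | 14.0 | 0.81 |
| 0.2 | 52.0% vs 64.4% | 12.4 | 0.72 |
| 0.3 | 58.0% vs 68.9% | 10.9 | 0.61 |
| 0.5 | 70.0% vs 77.8% | 7.8 | 0.39 |

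The rules can also disagree on whether there is an effect. Suppose 40% in each arm meet the Outcomes rule, and f is 20% off-site and 40% on-site (assumed). The 20a rates are 0.40 + 0.60 × 0.20 = 52% and 0.40 + 0.60 × 0.40 = 64%. The test rejects with probability 0.69, although the arms do not differ under the Outcomes rule.

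**4. The time frame.** The abstract gives a point (6 months); Objectives (7) and 20a give a period (0–6 months). Outcomes (12) uses both, which can be reconciled as a period outcome compared when the period ends.

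**5. The sampling clock.** Take six months as 26 weeks and a month as 4 weeks. On the text's clock, a person starting PrEP in week s is sampled at weeks s + 8, s + 12 and so on, up to week 26. The count is ⌊(18 − s)/4⌋ + 1 for s ≤ 18, and 0 after that. The last column reads Table 2's weeks from randomisation (8, 12, 16, 20, 26) and counts samples on or after the start.

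| PrEP start (week) | Samples, text's clock | Samples, Table 2 from randomisation |
|---|---|---|
| 0 | 5 | 5 |
| 4 | 4 | 5 |
| 8 | 3 | 5 |
| 12 | 2 | 4 |
| 16 | 1 | 3 |
| 20 | 0 | 2 |
| 24 | 0 | 1 |

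Table 2 does not state its origin, so the last column is one possible reading. Its baseline DBS cannot fit a schedule that begins 8 weeks after initiation.

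**The case against.** The strongest reply is that the 20a sentence is shorthand for a definition given in full under Outcomes (12), and that a journal article leaves operational detail to the analysis plan, which section 17a says will be finalised before data lock. This holds for two matters: whether all, any or the last sample must be detectable, and any concentration cut-off. Neither is counted here as an error. It does not hold for the definition itself, because the sentence that states the tested hypothesis gives a different criterion.

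A reader might go further and infer that the co-primary cannot show daily adherence on any reading, or that it is the same as the tertiary outcome. The article does not support that. The Outcomes rule requires self-reported daily use, and only the biomarker part coincides with the tertiary outcome, which also admits self-report of any use in any period. Under the Outcomes rule, daily use rests on self-report in an open-label trial. That is a limitation, not a contradiction.

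A reader might also infer that self-report is biased towards the on-site arm because adherence counselling is given there. Section 11c gives both arms up to five meetings meant to support adherence, so no direction can be claimed.

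On sampling, four text passages agree on the post-initiation clock, and the DBS row in Table 2 sits under a treatment subheading, so its weeks may be treatment weeks. It would therefore be too strong to say that Table 2 counts from baseline. What stands is the unexplained baseline DBS, the unlabelled origin, and a sample count tied to start date. It is also fair that someone starting after week 18 has hardly shown sustained use over six months.

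**Conclusion.** The point holds and should be settled before analysis. The two definitions cannot both be the co-primary, and under the 20a rule the outcome is recent PrEP use, not daily adherence. The abstract's time point conflicts with the period in the objectives and in 20a. The sampling schedule is not reconciled with Table 2.

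The size depends on how many people have detectable drug without reporting daily use, which the article does not give. For assumed shares of 10% to 50%, equal in both arms, power under the 20a rule runs from 0.81 to 0.39 instead of 0.89, provided that 40% and 55.5% describe the Outcomes rule. The stated power calculation itself is not wrong.

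The sample count of five down to none is arithmetic from the text's clock. It shows that measurement opportunity depends on speed of initiation. It does not show a bias of known direction or size between arms, because initiation times by arm and the rule for combining samples are not given.

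**What to change.** 1. Put one definition and one time frame in the abstract, Objectives (7), Outcomes (12) and 20a. The blinded investigators should fix it before data lock and before any outcome is tabulated by arm, since section 17a says the data analysts are not blinded.
2. Base it on the month-6 DBS already in Table 2, taken on all randomised participants whatever their PrEP start date. Make the monthly samples secondary, and state the origin of Table 2's week columns.
3. If the Outcomes (12) composite is kept, add self-reported daily use to the 20a hypothesis and report the biomarker-only result as a sensitivity analysis, because self-report is open-label. If the 20a rule is kept, call the outcome *recent PrEP use* and make no claim about daily adherence.
4. State in Sample size (14) which definition the 40% and 55.5% describe.
5. Keep any concentration-based analysis secondary and limited to participants not on HCV medication, as 20a already plans, since the article says protective norms on that medication are not established.
6. Table 4 already counts month 6 in long-term adherence; say how this overlap will be reported.

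The cost is mainly wording, plus a month-6 DBS for participants whom the text's schedule would not sample. The trial has been recruiting since September 2019, so check which participants past month 6 have that sample; one not taken cannot be recovered. A single month-6 sample says less about sustained use than a series, and the secondary monthly samples cover that.

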### Sample size (14)

We will utilize an alpha of .025 to account for our two co-primary outcomes. Our sample will include 500 participants in the PrEP component and approximately 240 in the HCV component. We estimated power using a simulation program written for SAS 9.4. This program generated data with various constellations of treatment effects, site effects, venue effects, and interactions. A simple power analysis shows that with 500 participants and alpha = .025 that there is 90% power to uncover an absolute difference of approximately 15% (40% versus 55.5%, RR = 1.40) for main effects of the treatment arm (across site and venue). This power statement assumes that response rates are at the point of highest variance in the binomial distribution—i.e., variance decreases causing power to increase if the probabilities are actually further from .5 in either direction. We anticipate larger absolute differences but have kept the simple power high to account for the potentially complex interactions we might see. For example, with this sample size, the power for the primary (PrEP) outcome is about 86.8% when there are differences in site and venue of 13% and 16% respectively, and when power for the site and venue differences is greater than 80%. There is better than 80% power for an interaction effect (e.g., site by treatment) with a rate ratio [RR(site 1)/RR(site2)] of at least 1.37. Power for effects within a site or venue is around 90% for an absolute risk difference of .22 (40% versus 62%). Note that planned tests of differences (i.e., interactions) by the biological variable, sex, would need to have a rate ratio of 1.5 to have 80% power. For HCV outcomes, the sample size is expected to be smaller (*n* = 240); for the HCV primary hypothesis, there is 90% power to uncover an absolute difference of 21% (40% versus 63%, RR = 1.58), well within the range of what we expect for this intervention [63]. This is based on the extremely low rates of PrEP currently in our candidate venues and the relatively high rate of continuation (58%) in the open-label extension of the Bangkok Tenofovir Study where PrEP was provided without cost as is the case in the current protocol [63].

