### Methods for additional analyses (e.g., subgroup analyses) (20b)

#### Mediators and moderators of outcomes

The difference in sustained PrEP adherence and HCV cure with on-site care relative to referral with patient navigation will be moderated by healthcare system and venue. As part of sensitivity analyses planned for all outcomes, we will examine differences in effects (moderation) with respect to the biological variable, sex, race/ethnicity, and various social determinants of health (e.g., housing instability, food insecurity, employment, income). We will document differences in risk profiles by these same characteristics (sex, race/ethnicity) as well as site and venue. All subgroups will be evaluated with a test of the interaction of the subgroup indicator and the treatment assignment.

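### The moderation sub-hypothesis is worded as a difference in rates but tested only as a ratio of risk ratios, and the two can disagree when control rates differ between settings

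*Protocol article*

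**What the plan says.** All references are to the protocol article.

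- **Hypothesis.** Statistical methods for primary and secondary outcomes (20a): "A sub-hypothesis is that the difference in rates of sustained PrEP adherence and HCV cure with on-site integrated care relative to referral" with navigation depends on health system and venue. It is directional: "differences between on-site versus referral will be greater in Miami vs. Montreal and in SSP vs. OAT settings". The section on mediators and moderators (20b) again speaks of the difference being moderated and names no scale.
- **Test.** Section 20a analyses both co-primary outcomes "using a Poisson regression analysis with a binary outcome to directly estimate the risk ratio associated with on-site integrated care". The same tests are stratified by site and venue, "testing for interactions of treatment effect by site and venue due to our expectation that context is important for implementation". No additive interaction is described.
- **Power.** Sample size (14): "There is better than 80% power for an interaction effect (e.g., site by treatment) with a rate ratio [RR(site 1)/RR(site2)] of at least 1.37". The same section describes effects within one site or venue additively, as a 22-point gain from 40% to 62%. Its worked example for the PrEP outcome has "differences in site and venue of 13% and 16% respectively".

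**The concern.** The hypothesis, read as written, has this null: on-site care adds the same number of percentage points in every setting. The interaction term of a log-link Poisson model tests another null: the risk ratio is the same in every setting. When on-site care works, both can be true only if control rates are equal across settings, and the protocol's own power example allows rates to differ by site and venue.

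The Objectives section (7) puts the contributions of city and venue in the same paragraph as the primary objective. Someone deciding where to place on-site care wants to know where it yields more additional adherent or cured people, which is an absolute quantity. A result on the ratio scale alone can misstate this, yet it would be reported as confirming a statement about differences.

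**Working it through.** **The plan's own figures.** Two-sided normal approximation with pooled variance under the null, alpha .025:

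- 40% vs 55.5%, 250 per arm: power 0.893 (stated 90%).
- 40% vs 62%, 125 per arm: power 0.898 (stated about 90%).
- Ratio of risk ratios 1.37: cannot be checked exactly, because the underlying rates are not given. With 125 per cell at two-sided .05, power is 41% if the comparison site is at 40%/55.5% and 86% if it is at 70%/70%. This figure is used here only to show which scale the interaction is on.

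**Inputs for the check.**

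- From the protocol: N = 500, 1:1 allocation, gain 55.5 − 40 = 15.5 points, and gaps of 13 and 16 points.
- Assumed: equal halves by site or venue (125 per cell), the gaps taken as control-rate gaps centred on 40%, and a two-sided test. No alpha is stated for the interaction, so .05 and .025 are both shown.

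**Why the scales separate.** With control rate c and absolute gain d, RR = 1 + d/c. For an equal positive d, the RR is larger wherever c is smaller.

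**Equal gain of 15.5 points, so the additive sub-hypothesis is false.** The test statistic is log(RR1/RR2), with variance equal to the sum over the four cells of (1 − p)/(125p).

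- *13-point gap:* 33.5% to 49% and 46.5% to 62%. RRs are 1.463 and 1.333, ratio 1.097, log 0.0926. Variance = (1.985 + 1.041 + 1.151 + 0.613)/125 = 0.0383, SE 0.196, standardized shift 0.473. P(declared greater in the lower-rate setting) = Φ(0.473 − 1.960) = 6.9% at .05, and Φ(0.473 − 2.241) = 3.8% at .025.
- *16-point gap:* 32% to 47.5% and 48% to 63.5%. RRs are 1.484 and 1.323, ratio 1.122, log 0.1152. Variance = (2.125 + 1.105 + 1.083 + 0.575)/125 = 0.0391, SE 0.198, shift 0.582. P = Φ(0.582 − 1.960) = 8.4% at .05, and Φ(0.582 − 2.241) = 4.9% at .025.
- The rates for a correct null are 2.5% and 1.25%. Binomial simulation with 200,000 replicates gave 6.6% and 8.0% at .05, and 3.6% and 4.5% at .025.

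**Converse.** With a common RR of 1.3875 and control rates of 33.5% and 46.5%, the gains are 13.0 and 18.0 points. The ratio interaction is exactly null although the differences in rates are unequal.

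**Sign reversal.** 25% to 38% is +13 points with RR 1.52. 50% to 66% is +16 points with RR 1.32. The first setting has the smaller difference and the larger ratio.

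**The case against.** The strongest reply is that the word difference is ordinary prose for the contrast between arms. The protocol writes absolute when it means additive, as it does in the sample size section, and it openly states interaction power as a ratio of risk ratios. On that reading the model, main effect and interaction share one scale, and a rejection under equal absolute gains is real heterogeneity on that scale. This part stands: the text is not a flat contradiction. But then the scale of a directional hypothesis phrased as a difference in rates is left to the reader, and the same clarification is needed.

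Three further points stand in full.

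- Main effects are examined if there is no qualitative interaction. That is a reversal of direction, and RR < 1 exactly when the risk difference is below zero, so this rule does not depend on scale.
- Cost-effectiveness is already assessed separately by city.
- The estimation technique could be left to an analysis plan. The scale of a stated hypothesis is less easily deferred once the article has fixed the hypothesis, the model and the interaction metric.

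A reader might infer more: that the test favours Miami and SSPs whenever their control rates are lower. The documents do not support that. A lower control rate gives no tilt under a common risk ratio or no effect. Nor does the protocol say that Miami or SSPs start lower. The 13 and 16 points are a power example with no direction, and they are not identified as control-arm rates. The study setting section describes venue resources, not adherence or cure. In Table 1 the Miami SSP has weekly physicians and HIV care on site, while the Montreal SSP lists no physicians. Much larger error rates can be produced, for example 44% rejection with control rates of 10% and 40%, but that gap appears nowhere in the protocol.

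**Conclusion.** The point holds as a mismatch between the wording of the sub-hypothesis and the scale of its only planned test. At gaps the size of the protocol's own example the effect is modest: risk-ratio ratios of 1.10 and 1.12, and a false finding of a greater effect in the lower-rate setting about 7–8% of the time at two-sided .05 (about 4–5% at .025) instead of 2.5% (1.25%). This rests on an equal 15.5-point gain, control rates centred on 40%, equal cells, and an additive reading of the hypothesis. The co-primary main-effect tests and their conclusions are untouched. What is exposed is the statement about where on-site care does more, which could be wrong in size or in sign if only the ratio is reported.

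**What to change.** - Keep the risk ratio for the main effect and keep the ratio-scale interaction.
- Add site and venue contrasts of risk differences, obtained as standardized risks from the same Poisson model with its arm-by-site and arm-by-venue terms, with delta-method or bootstrap intervals.
- Report control-arm rates by site and by venue beside them.
- State before data lock that a greater difference in rates in Miami or in SSPs will be claimed only if the risk-difference contrast supports it. Otherwise the finding is worded as a larger risk ratio.

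The cost is a few lines of text and code, and two interaction scales to report. The additive contrast also has low power. In the 13-point example its SE is √[(0.2228 + 0.2499 + 0.2488 + 0.2356)/125] = 0.0875, so 80% power at two-sided .05 needs gains that differ by about (1.960 + 0.842) × 0.0875 = 24.5 points. It should therefore be presented mainly as an estimate with its interval.
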